## Abstract

**Aims and Objectives:** To facilitate individualized assessment of unresponsive patients in the intensive care unit for signs of preserved consciousness after acute brain injury.

**Background:** Physicians and neuroscientists are increasingly recognizing a disturbing dilemma: Brain-injured patients who appear entirely unresponsive at the bedside may show signs of covert consciousness when examined by functional MRI (fMRI) or electroencephalography (EEG). According to a recent meta-analysis, roughly 15% of behaviorally unresponsive brain-injured patients can participate in mental tasks by modifying their brain activity during EEG- or fMRI-based paradigms, suggesting that they are conscious and misdiagnosed. This has major ethical and practical implications, including prognosis, treatment, resource allocation, and end-of-life decisions. However, EEG- or fMRI-based paradigms have so far typically been tested in chronic brain injury. Hence, as a novel approach, CONNECT-ME will import the full range of consciousness paradigms into neurocritical care.

**Methods:** We will assess intensive care patients with acute brain injury for preserved consciousness by serial and multimodal evaluation using active, passive and resting state fMRI and EEG paradigms, as well as state-of-the-art clinical techniques including pupillometry and sophisticated clinical rating scales such as the Coma Recovery Scale-Revised. In addition, we are establishing a biobank (blood, cerebrospinal fluid and brain tissue, where available) to facilitate future genomic and microbiomic research to search for signatures of consciousness recovery.

**Discussion:** We anticipate that this multimodal approach will add vital clinical information, including detection of preserved consciousness in patients previously thought of as unconscious, and improved (i.e., personalized) prognostication of individual patients. Our aim is two-fold: We wish to establish a cutting-edge tertiary care clinical service for unresponsive patients in the intensive care unit and lay the foundation for a fruitful multidisciplinary research environment for the study of consciousness in acute brain injury. Of note, CONNECT-ME will not only enhance our understanding of consciousness disorders in acute brain injury but it will also raise awareness for these patients who, for obvious reasons, have lacked a voice so far.

**Trial registration:** The study is registered with clinicaltrials.org (ClinicalTrials.gov Identifier: NCT02644265).

## Introduction

Searching for consciousness in patients with acute brain injury by means of clinical examination is difficult because patients must be awake, they must possess the voluntary drive to mobilize motor function, and this motor function must be preserved to a degree that is easily measurable. Moreover, consciousness levels fluctuate, and all these requirements need to be fulfilled at the time of examination (1–5) (Figure 1). Thus, many patients with disorders of consciousness (DoC) are incorrectly classified as being in a vegetative state (VS) (5). This has major ethical and practical implications for patients and their caregivers, including prognosis, treatment, resource allocation, and end-of-life decisions (6–10). For instance, most deaths (~70%) in the neuro-intensive care unit (ICU) occur following a decision to withdraw life-sustaining therapy (11), but the accuracy of current prognostic indicators and the evidence from controlled studies to guide decision-making are limited. This leads to a high risk of ‘self-fulfilling prophecy', i.e., misclassification of consciousness levels and premature prognostication, resulting in early withdrawal of life-sustaining therapy and death (12).

**Figure 1 F1:**
[figure not shown]
Correct evaluation of consciousness depends on the patient's behavior, which can be conceptualized as a product of arousal and motor output. Many patients with acute brain injury will only be aroused by certain stimuli and they lack motor output because of paralysis. In addition, their level of consciousness typically fluctuates with time. Thus, these patients are often wrongly believed to be unconscious. Our project CONNECT-ME will therefore employ serial and multimodal evaluations including state-of-the art fMRI and EEG technology in order detect covert consciousness in patients with acute brain injury. Adapted with permission from [name] et al. (1).

In order to circumvent the need for motor function, consciousness paradigms using functional magnetic resonance imaging (fMRI) and electroencephalography (EEG) have been developed (13–15). An estimated 15% of patients with a clinical diagnosis of VS can follow commands by performing mental imagery tasks when examined with fMRI and/or EEG paradigms, strongly suggesting that they are indeed conscious—at least every now and then (1). Accordingly, new concepts have emerged that defy established neurological practice such as the concept of cognitive motor dissociation (i.e., command following during fMRI and EEG despite being unresponsive at the bedside) (16). However, EEG- and fMRI-based paradigms have so far typically been tested in patients with chronic brain injury only, and the incidence of cognitive motor dissociation in the neuro-ICU is unknown (16).

Therefore, as a novel approach, *CONNECT-ME: Consciousness in neurocritical care cohort study using fMRI and EEG* (ClinicalTrials.gov Identifier: NCT02644265) is designed to import the full range of consciousness paradigms into neurocritical care. We aim to assess patients with acute brain injury for preserved consciousness by serial multimodal evaluations using active, passive and resting state fMRI- and EEG-based paradigms, as well as state-of-the art clinical rating scales and sophisticated bedside techniques such as pupillometry. Moreover, we are establishing a biobank (blood, cerebrospinal fluid, and feces) for genomic, metabolomic, and microbiomic research. All technological and scientific expertise is in place, including guidance by an International Scientific Advisory Board.

We anticipate that this approach will add essential clinical information, including detection of preserved consciousness in patients previously thought of as unconscious. The ability to identify preserved cognitive abilities following acute brain injury is of utmost importance to enable personalized diagnostics, to guide therapeutic decisions and to better predict outcome in non-responsive patients. This also represents an intriguing opportunity to institute focused rehabilitation early after the injury and to use rehabilitation resources in the most efficient way (17, 18).

The aim of CONNECT-ME is therefore two-fold: We wish to lay the foundation for a fruitful multidisciplinary research environment for the study of consciousness in acute brain injury, and at the same time, we will establish a cutting-edge tertiary care clinical service for unresponsive patients in the intensive care unit.

## Methods and design

The present protocol follows the requirements of the SPIRIT checklist (19).

### Research questions and objectives

We aim to establish, validate and improve fMRI- and EEG-based consciousness paradigms, as well as sophisticated clinical rating scales and bedside techniques such as pupillometry, for patients with acute brain injury in the ICU and step-down units. We will achieve this by using a multidisciplinary approach including expertise from neurology, neurosurgery clinical neurophysiology, anesthesiology, and functional neuroimaging. We hypothesize that serial multimodal assessments better reflect changing levels of consciousness than single unimodal evaluations. In addition, we wish to establish a biobank (blood, cerebrospinal fluid, and feces) for future genomic, metabolomic, and microbiomic research. Within 5 years, we will establish a full clinical service and a fruitful research milieu covering the entire spectrum of fMRI- and EEG-based consciousness paradigms in acute brain injury. Eventually, the present research project will lead to more efficient decision making in neurocritical care, thereby optimizing resource allocation and improving quality of life in survivors with decreased motor function because of acute brain injury.

#### Primary objectives

We aim to rigorously and systematically examine non-communicating patients with acute brain injury for preserved consciousness. To this end, we will set up fMRI- and EEG-based consciousness paradigms, implement standardized clinical rating scales into daily neurological routine and collect all relevant data in a prospective longitudinal database. Specifically, we wish to:
Establish and validate fMRI- and EEG-based consciousness paradigms in the ICU as well as in neurological and neurosurgical step-down units;Establish a clinical service for assessment of covert consciousness and cognitive abilities in non-communicating patients with acute brain injury who have lost motor output;Establish a biobank (blood, cerebrospinal fluid, and feces) for genomic, metabolomic, and microbiomic research;Establish a fruitful research environment on fMRI- and EEG-based consciousness paradigms in acute brain injury.

#### Secondary objectives

We wish to pool fMRI- and EEG-based data as well as results from systematic clinical evaluations and genomic and metabolomic data to study the neuronal mechanisms by which patients regain consciousness following acute brain injury.

We will test the following hypotheses:
fMRI- and EEG-based consciousness paradigms are feasible in patients with complete (or near-complete) loss of motor function in the acute phase of brain injury.fMRI- and EEG-based consciousness paradigms, including state-of-the-art clinical rating scales and bedside techniques such as pupillometry, applied in the acute phase of brain injury, will add clinically relevant information that complements standard bedside examination. This includes detection of preserved consciousness in some patients who were clinically classified as being unconscious due to lost motor output.fMRI- and EEG-based consciousness paradigms do not always yield the same evidence for the presence or absence of consciousness in acute brain injury.Serial multimodal evaluations will better reflect a changing level of consciousness than single unimodal assessments.In most patients who regain consciousness after acute brain injury, the following pattern will be observed: Intrinsic cortical connectivity, including fronto-parietal networks, as revealed by resting state paradigms will recover first, followed by the occurrence of cognitive evoked potentials and cortical activation (passive paradigms), and lastly, the ability to follow commands (active paradigms).Because of the absence of a gold standard for consciousness (1), a composite reference standard, considering bedside examination, clinical rating scales and fMRI- and EEG-based consciousness paradigms, allows the most reliable classification of patients with DoC (16).Genomic and metabolomic data may reveal signatures for consciousness recovery.

### Target condition, outcome measures, inclusion, and exclusion criteria

We define the target condition (*primary outcome*) as signs of preserved consciousness in non-communicating patients with DoC due to traumatic brain injury (TBI) or non-traumatic TBI, including (but not limited to) cerebrovascular disorders (CVA; including ischemic and hemorrhagic stroke, subarachnoid hemorrhage, and cerebral venous sinus thrombosis), anoxic-ischemic encephalopathy (e.g., due to cardiac arrest), and neuroinflammatory conditions (e.g., autoimmune encephalitides, neuroinfectious disease). The target condition will be assessed using clinical evaluation as well as fMRI- and EEG-based consciousness paradigms (*outcome measures*), including command following (active paradigms), preserved cognitive evoked potentials or cortical activation (passive paradigms; fMRI, respectively, EEG), and intrinsic functional connectivity, including the auditory and default mode networks (resting state paradigms). Results from fMRI- and EEG-based consciousness paradigms will be analyzed for similarities and dissimilarities and correlated with clinical data from standardized bedside examination and clinical rating scales to learn about the neuronal mechanisms by which patients recover consciousness following acute brain injury (*secondary outcomes*).

#### Target population

Our target population consists of adult non-communicating patients with DoC due to TBI and non-TBI (age >15 years). We apply the classical definition of consciousness as a “state of full awareness of the self and one's relationship to the environment” (20).

#### Inclusion criteria

Inclusion criteria include non-responding patients (clinically defined as coma, VS/unresponsive wakefulness syndrome (UWS), minimal conscious state (MCS), emerged from MCS (eMCS), or locked-in syndrome) with acute or sub-acute (arbitrarily defined as ≤ 31 days from injury) TBI or non-TBI, needing structural MRI for clinical reasons (diagnosis, prognostication). The great majority of these patients will be intubated on ventilatory support. We will aim for unsedated patients. However, if patients cannot be weaned from sedation, the level of sedation will be lowered to the lowest possible level.

#### Exclusion criteria

Exclusion criteria include contraindications for examination by MRI, severe cardiorespiratory compromise and similar acutely life-threatening conditions, evidence of severe pre-morbid neurological deficits such as aphasia or deafness, lack of Danish or English language proficiency, age <15 years, and evidence of defect auditory and sensory pathways [if clinically suspected or as revealed by pretest screening with brainstem auditory evoked potentials (BAEP) and somatosensory evoked potentials (SSEP)]. Sedation is an important confounder during fMRI scans that must be carefully monitored; we will therefore also exclude patients requiring sedation levels exceeding 1 mg/kg/h propofol at baseline. Although we will aim for no sedation or the lowest possible level of sedation to reduce movement artifacts, we will leave the choice of the sedative drug and the dosage to the discretion of the responsible anesthetist. [Fortunately, recent studies indicate that connectivity decreases associated with propofol and sevoflurane sedation, involving the thalamus and insula, are relatively small compared with those already caused by structural brain injury (21, 22)].

#### Definitions

The term DoC includes patients in coma, VS/UWS, and MCS, as well as those who have emerged—but not completely—from MCS (eMCS). *Coma* may be defined as a state of profound unawareness from which patients cannot be aroused. Crucially, a normal sleep-wake cycle is absent. This lasts usually only a few days to 3 weeks following acute brain injury. In contrast, the *VS/UWS*, is a condition of wakefulness without awareness (4). Patients in this condition may open their eyes but exhibit only reflex behaviors and are therefore considered unaware of themselves and their surroundings. In comparison, patients in *MCS* show unequivocal signs of non-reflex behaviors occurring inconsistently, yet reproducibly, in response to environmental stimuli. Although some may follow commands to a certain degree, accurate communication is not possible. VS/UWS and MCS most likely exist on a spectrum rather than being categorically distinct (23, 24). Thus, patients may be classified into MCS plus (i.e., if they are able to obey commands) or minus (i.e., if they only localize pain, exhibit visual pursuit or show appropriate emotional expressions) (25). Traditionally, VS/UWS has been considered permanent 3 months after non-traumatic injuries and 12 months following TBI but late recovery is increasingly recognized (4). [A recent guideline committee therefore suggested that the term ”permanent” should be abandoned (26)]. Patients may evolve from VS/UWS into MCS (or better) and they may or may not relapse. It follows that signs of preserved consciousness can wax and wane (Figure 1).

#### Neurological bedside examination and clinical rating scales

Patients will be assessed using a detailed neurological bedside exam performed by or supervised by board-certified neurologists with experience in neurocritical care. Patients will be examined by standardized clinical rating scales, including (but not limited to) Glasgow Coma Scale (GCS), Full Outline of UnResponsiveness (FOUR), and Coma Recovery Scale-Revised (CRS-R) (27). Examinations will be performed daily on the ward as well as directly (within 30 min) prior and after each fMRI and EEG session.

#### fMRI- and EEG-based consciousness paradigms (active, passive, and resting state)

Whereas, active paradigms of consciousness may suggest a higher degree of certainty, passive, and resting state paradigms should also allow detecting signs of consciousness in patients who are not able to cooperate in cognitive tasks because of aphasia, neglect, executive dysfunction, major depression or deafness (1). Indeed, in a recent landmark study, it was shown that intrinsic functional connectivity assessed by fMRI, including (but not limited to) the auditory and default mode networks, may differentiate MCS from VS/UWS at the single-patient level (28). Thus, as stated above, we will establish the full range of fMRI- and EEG-based paradigms, including active, passive, and resting state paradigms.

### Study design and setting

The study will be performed at the Neurocentret, Rigshospitalet, Copenhagen University Hospital, with input from the departments of neurology, neurosurgery, clinical neurophysiology, neuroanesthesiology, and radiology, as well as the Neurobiology Research Unit (University of Copenhagen). To facilitate this complex project in the most efficient way, we have divided it into 9 work packages (Figure 2). Work packages 1–2 cover the first phase of the project (set-up), work package 3–8 covers the second phase (clinical implementation) and work package 9 covers the third phase (clinical routine). The vision is that once work package 9 has started, CONNECT-ME will transform into a fully functional tertiary care patient service and enable ongoing prospective data acquisition for clinical research purposes.

**Figure 2 F2:**
[figure not shown]
Schematic overview of the work packages and timeline of the project.

#### Work package 1 (resting state fMRI; resting state EEG, clinical protocol)

Enrollment began on April 12, 2017 (24 patients have been enrolled as of September 1, 2018). We are evaluating a convenience sample of DoC patients with acute brain injury (*n* = 24), admitted to the ICU and/or neurological and neurosurgical step-down units, using resting state fMRI and EEG. Relevant protocols are established at our institution. Pilot data from a previous cohort on resting state fMRI have been published (21).

##### fMRI

Resting-state fMRI are performed on a 3T Prisma MRI scanner with 64-channel head coil. Despite altered states of consciousness, participants are instructed to close their eyes and let their mind wander, but not to fall asleep. During the procedure, patients are monitored by an experienced neuroanesthesiologist and a nurse anesthetist; patients are sedated, if necessary, with sevoflurane or propofol at low doses for optimal image acquisition and mechanically ventilated aiming at normal ventilation. Participants complete a 10-min T2^*^-weighted echo-planar imaging BOLD fMRI sequence (no. of volumes = 300 volumes, TR/TE = 2,000/30 ms, flip angle = 90°, in-plane matrix 64 × 64, number of slices = 32, voxel size = 3.6 × 3.6 × 3.75 mm). A high-resolution 3D T1- weighted structural image is acquired using a sagittal, magnetization prepared rapid gradient echo (MP-RAGE) sequence (TR/TE/TI = 1,900/2.58/900 ms, flip angle = 9°, in-plane matrix 256 × 256, number of slices = 224, voxel size = 0.9 × 0.9 × 0.9 mm). We use single-subject seed-based analysis to estimate seed-to-voxel and seed-to-seed connectivity. Functional imaging data are pre-processed using SPM12 (https://www.fil.ion.ucl.ac.uk/spm/software/spm12/) and Conn v16.b (29). We will visually inspect all acquired scans to assess data quality and document morphological abnormalities that may introduce noise. We account for physiological and other noise sources using methods typically applied to resting-state fMRI data. This includes applying a bandpass filter (range 0.008–0.09 Hz) and denoising gray-matter voxel time series using aCompCor (30). We will quantify default-mode network and other canonical resting-state networks using regions defined from an independent dataset (e.g., “networks” region set in Conn). We use Fisher's r-to-z transformation to convert the estimated correlation coefficient (rho) between any of two means, denoised time series. Qualitative assessment of the presence of DMN (21) and other networks will be complemented by data-driven strategies, including defining deviation from normal DMN connectivity defined as a multivariate distribution based on a reference healthy control population that has been scanned on the same MRI using scan parameters identical to those we use here (31). Investigators classifying the DMN are blinded to clinical outcome.

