##### EEG

EEG will be recorded using standard clinical procedures including a 28-channel system and video observations within 1 h before or after fMRI (or as close to this time as possible) and read by board-certified electroencephalographers with experience in neurocritical care EEG. Artifacts such as those due to excessive muscular activity will be dealt with according to standard clinical procedures (e.g., adjustment of EEG equipment, removing sources of noise from the environment, post-processual data cleansing). We will assess EEG background activity and EEG reactivity both by visual and by spectral EEG analysis, including absolute and relative EEG power in different frequency bands. *EEG background activity:* Ten minutes of resting state EEG with the patient in a quiet environment will be analyzed; artifacts in the ICU settings such as background noise will be dealt with and prevented (if possible) according to standard clinical procedures. In addition to visual EEG analysis by board-certified electroencephalographers, 2x6 10 s artifact-free EEG segments will be compared pairwise and analyzed using EEG spectral analysis to assess for spontaneous fluctuations in the background activity (which allows us to distinguish between spontaneous fluctuations and evoked reactive EEG changes following external stimuli during subsequent reactivity testing). *Reactivity:* EEG reactivity is defined as any change in frequency or amplitude of the EEG background activity resulting from a specific external stimulus (32). However, although different methods exist to assess EEG reactivity, all those methods are poorly validated (or not at all). In a recent review, Azabou et al. analyzed more than 200 studies and concluded that current assessment methods are very heterogeneous, and that consensus for standardizations of stimulations and interpretations is absent (33). Therefore, we will use a battery of easy-to-implement stimulations and evaluate EEG reactivity both visually and using spectral EEG analysis, which will reduce interrater variability. To test EEG reactivity, we will apply auditory, sensory and nociceptive stimuli as well as eye opening. Each stimulation will be analyzed and graded for presence or absence of reactivity in the EEG background. Auditory stimulation by calling the patient by their own name has been shown to elicit a robust electrophysiological response, especially when involving a familiar voice (34). Further, we will apply nociceptive (10 s of compression of the earlobes bilaterally), sensory (light touch involving the external openings of the nostrils) and visual stimulation (passive eye opening/eye closure). All procedures will be performed by trained EEG technicians supervised by the CONNECT-ME study team. Absolute total and relative power will be evaluated in the delta (1–4 Hz), theta (4–8 Hz), alpha (8–13 Hz), beta (13–30 Hz), and gamma (>30Hz) bands and averaged within each EEG channel. For detailed analysis the electrodes will be grouped into four regions of interest: fronto-central (Fp1, Fp2, F3, F4, C3, C4), temporal (F7, F8, T7, T8, P7, P8), parieto-occipital (P3, P4, O1, O2), and midline (Fz, Cz, Pz). EEG patterns will be classified according to Synek's scale (35). In addition to conventional analyses and once a sufficient number of patients has been included (~from 50 patients onwards), we will aim for data-driven approaches as well, using machine learning paradigms, to search for EEG markers of consciousness such as recently proposed (36–38).

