
#### Work package 2 (clinical database, biobank)

To maximize the learning effect and to facilitate research, we will collect all relevant clinical, neurophysiological and imaging data in a comprehensive longitudinal database. This database is currently being developed, using REDCap which is provided free of charge to health care providers within the Capital Region of Denmark (45). At present, the database consists of 11 instruments (*Study ID; Cause of ICU admission; Baseline Data at ICU admission; Laboratory investigations; Neurological exam; MRI, including fMRI; EEG; Pupillometry; Neurological exam and data at ICU discharge; 3 months follow-up; and 12 months follow-up*) and at total of 555 fields (= questions). For a given patient, only a subset of these fields needs to be answered, depending on the diagnosis at admission and initial diagnostic procedures. Clinical outcome data will be assessed by a trained research nurse and a clinical PhD student, either by telephone interview or during follow up visits, using established rating scales (e.g., Coma Recovery Scale-Revised, modified Rankin Scale, Barthel index) at hospital discharge and at 3, respectively, 12 months. Target clinical data include (but are not limited to): age, sex, previous medical history (including hereditary predispositions), medication (including drugs with potential influence on consciousness levels such as antiepileptics or antidepressants), cause of admission, sedation, surgical and non-surgical complications, comprehensive laboratory investigations, neurological examination, CRS-R, GCS, FOUR, and outcome data including modified Rankin Scale (mRS), Barthel index, Glasgow Outcome Scale (GOS), as well as whether at follow-up the patient lives at home, is admitted to a rehabilitation facility, or resides in a nursing home. Neurophysiological data include (but are not limited to) resting state, passive and active EEG paradigms and (where appropriate) evoked potentials, including SSEP and BAEP. Imaging data include data from resting state, passive and active fMRI paradigms and structural MRI, including (but not limited to) T1- and T2-weighted imaging, DWI, FLAIR, gradient echo sequences and (where appropriate) MR spectroscopy and tractography. In addition, we are setting up a biobank for cerebrospinal fluid, blood and feces samples for future studies related to genomics, metabolomics and microbiomics. Minus 80° freezer facilities are available at our institution.

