### Statistical analysis

A power calculation of the required sample size that would include the combined different methods does not appear feasible owing to the multimodal design of CONNECT-ME but the numbers of patients recruited into the different work packages reflects empirical numbers derived from previous results on consciousness paradigms in the critical care setting (21, 47). In addition to descriptive statistics, we will perform correlation analysis between behavioral scales (CRS-R total score) and default mode networks, respectively, EEG entropy using Spearman testing. Non-parametric tests will be used for univariate analysis (Wilcoxon rank sum/Mann-Whitney test and Kruskal-Wallis test) to test whether default mode and other brain networks or EEG entropy differ between diagnostic groups (VS/UWS vs. MCS). Machine learning models will be applied to evaluate resting-state fMRI and other neuroimaging measures as predictors of covert consciousness and subsequent recovery (i.e., does imaging data inform patient level of consciousness and/or prognosis). Receiver operating characteristic (ROC) analysis may be used to identify a cut-off value differentiating conscious (MCS) from unconscious (coma or VS/UWS) patients. Results will be considered significant at *p* < 0.05 or lower, if appropriate (e.g., <0.001 for fMRI data). Statistical advice and supervision, including exploration with advanced machine learning algorithms, will be provided in-house (Department of Biomedical Statistics, University of Copenhagen).

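### The stated blinding of DMN raters covers later outcome but not the concurrent CRS-R score and bedside diagnosis that the planned tests compare the DMN with

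*Protocol article*

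**What the plan says.** In the fMRI part of work package 1, the DMN is assessed in two ways. One is a reader's judgement, which the article supplements: "Qualitative assessment of the presence of DMN (21) and other networks will be complemented by data-driven strategies". The other is computed: "We will quantify default-mode network and other canonical resting-state networks using regions defined from an independent dataset". The same paragraph ends with the only reader-blinding rule in the article: "Investigators classifying the DMN are blinded to clinical outcome".

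Work package 2 says when outcome is scored: at hospital discharge and at 3 and 12 months, on scales that include the CRS-R, the modified Rankin Scale and the Barthel index.

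The Statistical analysis section names the comparisons. In its words, "we will perform correlation analysis between behavioral scales (CRS-R total score) and default mode networks, respectively, EEG entropy using Spearman testing". Rank tests then compare brain networks and EEG entropy between VS/UWS and MCS, and ROC analysis may be used to "identify a cut-off value differentiating conscious (MCS) from unconscious (coma or VS/UWS) patients".

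The section on bedside examination and clinical rating scales schedules examinations daily and within 30 minutes before and after each fMRI and EEG session. (Work package 4 says 60 minutes for its fMRI assessments; the difference does not affect this point.)

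**The concern.** A reader who must decide whether a network is present in a damaged brain will meet borderline scans. If that reader knows the patient was scored as VS/UWS or MCS around the time of the scan, borderline calls can move toward that label. The later test of the call against the label then partly measures what the reader already knew.

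Two results are at stake, and the bias affects them differently:

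- The association between DMN and CRS-R, and the separation of VS/UWS from MCS, would look stronger than they are.
- Disagreement between bedside and scan would look rarer than it is. The secondary objectives expect to find preserved consciousness in some patients classed clinically as unconscious, and expect fMRI and EEG sometimes to disagree. The secondary outcomes are the similarities and dissimilarities between modalities and their correlation with bedside data. Readings pulled toward the bedside label, or toward the other modality, work against these aims.

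**Working it through.** No arithmetic applies: no figure in the article depends on blinding, and none gives the size of a reading bias. The check sets the stated rule beside the stated analysis.

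1. **What the raters are masked to.** The fMRI paragraph says clinical outcome and names nothing else.
2. **What clinical outcome means.** Work package 2 ties it to discharge, 3 months and 12 months. A CRS-R score taken at those times is therefore covered. A CRS-R score taken around the scan is not outcome data in this sense.
3. **What the DMN is tested against.** The Statistical analysis section names the CRS-R total score, VS/UWS versus MCS, and MCS versus coma or VS/UWS. These describe the patient's current state.
4. **When that reference exists.** Bedside scales are due within 30 minutes on either side of the session. Visual classification follows acquisition and, for the processed networks, denoising. The bedside score is thus normally on record when the scan is classified.
5. **Whether the rule covers the comparison.**

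| Comparison | Reference | Covered by the stated rule |
|---|---|---|
| DMN and recovery | Scales at discharge, 3 and 12 months | Yes, on the scan-reading side |
| DMN and CRS-R total score | CRS-R around the scan | No |
| DMN in VS/UWS versus MCS | Bedside diagnosis around the scan | No |
| ROC cut-off, MCS versus coma or VS/UWS | Bedside diagnosis around the scan | No |

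6. **Which measures are open to judgement.** The qualitative DMN call is. So is the visual grading of EEG background and reactivity, where each stimulation is graded for presence or absence; the EEG paragraph itself describes existing reactivity methods as poorly validated. Connectivity from predefined regions, spectral power and EEG entropy are computed and much less exposed.
7. **Which DMN measure enters the tests.** The Statistical analysis section does not say whether it is the qualitative call, the computed connectivity or both.
8. **Scale.** Work package 1 has 24 patients, so each changed call is 1/24 = 4.2% of that sample. How many calls would change cannot be derived.
9. **The other direction.** The Discussion says in one place that a summary of results goes to treating physicians on request during work packages 1-8. In another it says that results reach attending clinicians only after the relevant work packages are complete. Read together, these do not settle whether bedside examiners could know earlier paradigm results.

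**The case against.** The strongest reply has four parts.

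**Silence is not unblinding.** The article does not say that DMN raters know the CRS-R or the diagnosis, and a condensed article may leave masking details to the full protocol. The first half stands: the finding is that independence is not assured, not that it is absent. The second half carries less weight, because the article does not leave this rule out. It states a rule, and the target of that rule does not match the comparison the article then plans.

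**The tested variables may be computed ones.** EEG entropy is computed, the DMN is quantified from predefined regions, and rank correlation and ROC cut-offs suit graded measures better than a present/absent call. This stands in part. If only computed connectivity entered the tests, the exposure would be small. But the article presents the qualitative assessment as the approach that the data-driven strategies complement, and does not exclude it from the tests.

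**EEG readers and video.** A reader might infer that electroencephalographers watch the patient's behaviour while grading, because "EEG will be recorded using standard clinical procedures including a 28-channel system and video observations". The text describes recording. It does not say that video is viewed during grading, and EEG-reader masking is not addressed at all. That inference is not supported.

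**Outcome assessors.** A reader might also infer that follow-up is scored with knowledge of the scan, because "Clinical outcome data will be assessed by a trained research nurse and a clinical PhD student" and no masking is mentioned. The text names the assessors and says nothing either way, so no claim of unmasked follow-up can be made.

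**Conclusion.** The point holds in limited form. The one stated reader-blinding rule protects the comparison of DMN with later outcome, while the named diagnostic tests use a bedside reference obtained around the scan, which the rule does not reach. For the qualitative DMN classification, independence from that reference is not assured.

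This rests on two assumptions: that the qualitative call enters at least some of the comparisons, and that raters could have access to the bedside score. The article neither confirms nor excludes either.

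The likely direction is toward the known diagnosis. This would inflate the association between DMN and CRS-R and understate discordance between bedside and fMRI. The size cannot be stated: any odds ratio or bias rate would need inputs the documents do not give. The conclusion does not extend to computed connectivity or EEG entropy in the same degree, and the text does not support reading it as proof that the readings are dependent.

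This should be corrected, because the remedy is cheap and the exposed comparison is central to the study.

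**What to change.** Replace the blinding sentence in the fMRI paragraph with one to this effect: investigators classifying the DMN read coded scans and are blinded to the concurrent CRS-R score, the bedside diagnosis, the EEG result and clinical outcome.

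In the EEG paragraph, apply the same rule to the visual grading of background and reactivity, with the fMRI result in place of the EEG result.

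Work package 1 scans that were classified without this masking can be re-read from coded files.

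Reconcile the two Discussion statements on releasing results to physicians during work packages 1-8, so that it is clear what bedside examiners may know.

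The cost is some file coding by existing staff, slightly slower reading, and a second read of up to 24 work package 1 scans. No change to recruitment, acquisition or the planned tests is needed.
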